## Demographic and Baseline Characteristics

The following demographic variables at screening will be summarized by intervention groups: gender, age, height, weight, BMI. The following day of surgery characteristics will be recorded on the day of surgery: surgeon performing surgery, duration of surgery, conversion to open surgery.

## Analysis of Primary Endpoint

This study is designed as a prospective two treatment parallel-design study. The primary outcome is the time to block onset. Time-to-event data will be compared using the log-rank test.

## Analysis of Secondary Endpoints

Categorical data will be analyzed using Chi squared analysis or Fischer's exact test, depending on sample size. Comparison of means will be performed using the independent sample t-test or the Mann-Whitney U test, depending on distribution. A p-value of 0.05 or smaller will be considered statistically significant.

Safety and tolerability data will be summarized by treatment group. Adverse event rates will be coded by body system and MedDra classification term.  Adverse events will be tabulated by treatment group and will include the number of patients for whom the event occurred, the rate of occurrence, and the severity and relationship to study drug.

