| **SECONDARY OBJECTIVES** | We hypothesize that the intraplexus approach will have a longer block duration, thus leading to reduced opioid consumption and greater  patient satisfaction postoperatively. We also hypothesize that the intraplexus technique will need to a faster procedure time, thus improving efficiency.  Secondary outcome variables that we will also investigate include: time to onset of sensory block, duration of nerve blockade, highest NRS pain score in the post anesthesia recovery unit and  postoperative day 1, block performance time, patient satisfaction score, perioperative opioid use, perioperative analgesic consumption, incidence of paresthesias, number of needle passes, incidence of postoperative nausea, vomiting, constipation, and any other complications. |
|  |  |
| **NUMBER OF SUBJECTS** | 208 |
|  |  |
| **SUBJECT SELECTION**  **CRITERIA** | Inclusion Criteria:  Age at least 18 years old, ASA I-II classification, scheduled for shoulder surgery  Exclusion Criteria:  Age younger than 18, non-English speaking, any contraindication for regional anesthesia, such as allergy to local anesthetics or opioids, coagulopathy or severe thrombocytopenia, infection at  puncture sites, pre-existing neuropathy in operative limb, need for postoperative nerve function monitoring, pulmonary disease or low baseline oxygen saturation, dementia, patient refusal, and high preoperative opioid requirements. |
|  |  |
| **TEST PRODUCT, DOSE, AND ROUTE OF ADMINISTRATION** | *25mL Ropivacaine 0.5% will be administered once via intraplexus brachial plexus block.* |
|  |  |
| **CONTROL PRODUCT, DOSE AND ROUTE OF ADMINISTRATION** | *25mL Ropivacaine 0.5% will be administered via extraplexus brachial plexus block.* |
|  |  |
| dURATION OF SUBJECT PARTICIPATION AND DURATION OF STUDY | Subjects will be on study for up to 15 days  **Screening:** up to 7 days  **Treatment:** 1 day  **Follow-up:** 7 days  The total duration of the study is expected to be 2 years. 24 months for subject recruitment and 24 months for final subject follow-up. |
| **E** |  |
| **CONCOMMITANT MEDICATIONS** | Allowed: midazolam, fentanyl, lidocaine, propofol, sevoflurane, desflurane, dexamethasone, ondansetron, prochlorperazine, metoclopramide, meperidine  Prohibited: Hydromorphone, ketorolac |
|  |  |
| **Efficacy Evaluations** |  |
| ***Primary endpoint*** | - Time to onset of motor block (loss of shoulder abduction) |

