| ***Secondary endpoints*** | - Time to onset of sensory block - Duration of nerve blockade - Highest pain score in the post-anesthesia recovery - Highest pain score on post operative day 1 - Block performance time - Patient satisfaction score - Perioperative opioid use - Perioperative analgesic consumption - Number of needle passes - Block failure - Recovery room length of stay - Incidence of postoperative nausea, vomiting, constipation, and any other complications (hoarseness, shortness of breath, Horner’s syndrome, nerve injury, local anesthetic toxicity, infection at insertion site) - Incidence of paresthesias |
| **Safety Evaluations** | Incidence of adverse events will be recorded and monitored during the study. |
| **Planned Interim Analyses** | Serious adverse events will be monitored by an independent data monitoring committee on an ongoing basis throughout the study. |
|  |  |
| **STATISTICS**  **Primary Analysis Plan** | This study is designed as a prospective two treatment parallel-design study. The primary outcome is the time to block onset. Time-to-event data will be compared using the log-rank test. Assuming a true hazard  ratio of 0.65, power of 0.8 and alpha of 0.05, a sample size of 104 patients per group is needed. This is based on the assumption that the total number of events will be 172. |
| **Rationale for Number of Subjects** | The estimated sample size for a two-sample comparison of survivor functions for the primary outcome variable of time to onset of motor block using the Freedman method for log-rank test with a hazard ratio of 0.65, Power of 0.8 and alpha of 0.05, was a total of 208 patients for the two groups, assuming a total number of 172 events. |

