## Secondary Objectives

- Time to onset of sensory block
- Duration of nerve blockade
- Highest pain score in the post-anesthesia recovery
- Highest pain score on postoperative day 1 and at postoperative week 1
- Block performance time
- Patient satisfaction score
- Perioperative opioid use
- Perioperative analgesic consumption
- Number of needle passes
- Block failure
- Recovery room length of stay
- Incidence of postoperative nausea, vomiting, constipation, and any other complications (hoarseness, shortness of breath, Horner’s syndrome, nerve injury, local anesthetic toxicity, infection at insertion site)
- Incidence of paresthesias

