## Secondary Efficacy Endpoints

- Time to onset of sensory block – evaluated by detection of decreased sharpness of contralateral side. This will be evaluated for supraclavicular, axillary, musculocutaneous, median and ulnar nerve distributions.
- Duration of nerve blockade (time from block completion to time patient reports the block started to wear off and no longer providing pain relief)
- Highest pain score in the post-anesthesia recovery unit (using numerical rating scale from 0-10 pain, 0 is no pain, 10 is worst imaginable pain)
- Highest pain score on postoperative day 1 (using numerical rating scale from 0-10 pain, 0 is no pain, 10 is worst imaginable pain), at rest and with movement
- Block performance time - time from block needle insertion to the time that all of the local anesthetic was injected
- Patient satisfaction score – scale from 0-10. Zero is unsatisfied. 5 is neutral and 10 is extremely satisfied.
- Perioperative opioid use – total opioids used preoperative, intraoperative, and postoperatively will be recorded
- Perioperative analgesic consumption – acetaminophen, ibuprofen, ketorolac usage perioperatively
- Number of needle passes - number of times the needle was re-advanced after being withdrawn during block placement
- Block failure - lack of sensory exam consistent with interscalene block in the recovery room or need for repeat interscalene block in recovery room
- Recovery room length of stay (time from entering recovery room to time that discharge criteria met)
- Highest pain score at one week postoperative week visit (0-10 with zero being no pain and 10 worst imaginable pain)

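### An unadjusted 0.05 significance rule covers about 11 to 13 secondary endpoints, with no testing order or exploratory label

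*Protocol*

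**What the plan says.** The subsection Analysis of Secondary Endpoints names the tests and then the criterion. For categorical outcomes: "Categorical data will be analyzed using Chi squared analysis or Fischer's exact test, depending on sample size". For continuous outcomes: "Comparison of means will be performed using the independent sample t-test or the Mann-Whitney U test, depending on distribution". The criterion follows directly: "A p-value of 0.05 or smaller will be considered statistically significant". Nothing in the protocol limits how many tests this covers, orders them, picks out a key secondary endpoint or calls the results exploratory.

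The endpoints are listed three times, with different counts:

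- The synopsis has 13 bullets, starting with sensory onset and ending with complications and paresthesias.
- The body section Secondary Objectives also has 13 bullets, but one of them holds two variables: "Highest pain score on postoperative day 1 and at postoperative week 1".
- The section Secondary Efficacy Endpoints has 12 bullets. It adds "Highest pain score at one week postoperative week visit" and leaves out complications and paresthesias, which appear under Safety Evaluations instead.

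The second paragraph of Analysis of Secondary Endpoints says that safety data will be summarised and tabulated by group, and names no test for them.

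The synopsis also states directional hypotheses: "We hypothesize that the intraplexus approach will have a longer block duration", followed by lower opioid consumption, greater satisfaction and a faster procedure. The analysis section does not treat these four differently from the rest.

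**The concern.** The protocol states a criterion here. As written, any secondary endpoint at or below 0.05 may be reported as statistically significant, whatever happens on the primary endpoint and however many other endpoints were tested.

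The situation in which this matters is foreseeable. The protocol's own overview of clinical studies describes an earlier interscalene trial that found no difference in onset but a significantly longer block in the subfascial group. If this trial also finds no difference in onset, readers will look to the secondary endpoints. Under the present rule a result on block duration, which was hypothesised in advance, would carry the same label as a result on any other item that happened to cross 0.05. At stake is how far a secondary finding can be trusted, and how the trial may describe it.

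**Working it through.** **The plan's own figures.** The protocol gives no error rate for the secondary endpoints as a group, so there is none to reproduce. The only design figure with an alpha belongs to the primary endpoint: 172 events for a hazard ratio of 0.65, power 0.8 and alpha 0.05. With two-sided 0.05, Freedman's formula gives 175 events and Schoenfeld's gives 170, both within 2% of 172. The one-sided versions give 138 and 134 and do not match. The protocol does not state sidedness, so two-sided tests are assumed below.

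**Number of tests, k.**

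- The 13 synopsis bullets give k = 13.
- Taking out complications and paresthesias as safety items gives k = 13 − 2 = 11.
- The Secondary Efficacy Endpoints list, which adds week 1 pain, gives k = 12.
- Keeping the two safety items and adding week 1 pain gives k = 14, the most that the lists allow without splitting items.

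**Chance of at least one significant result in either direction, no true difference on any endpoint, independent tests.** The formula is 1 − 0.95^k.

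| k | 1 − 0.95^k |
| --- | --- |
| 4 (the hypothesised outcomes only) | 0.185 |
| 11 | 0.431 |
| 12 | 0.460 |
| 13 | 0.487 |
| 14 | 0.512 |

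**Correlated tests.** The protocol gives no correlations, so a range is assumed. A simulation of 13 two-sided z-tests with a common correlation (200,000 draws, no true difference) gave:

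| Common correlation | Chance of at least one p ≤ 0.05 |
| --- | --- |
| 0.1 | 0.48 |
| 0.2 | 0.45 |
| 0.3 | 0.42 |
| 0.5 | 0.34 |
| 0.7 | 0.24 |

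**False results favouring intraplexus only.** A two-sided test at 0.05 puts 0.025 in each direction. With independent tests, 13 endpoints give 1 − 0.975^13 = 1 − 0.720 = 0.280, and 11 give 1 − 0.975^11 = 1 − 0.757 = 0.243. Positive correlation would be expected to lower both.

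**The case against.** The strongest reply is that the protocol announces a detailed SAP, which is to contain any modifications to the plan. Multiplicity for secondary endpoints is often settled there. On this view 0.05 is only a conventional per-test threshold and no claim rests on it. This stands in part: the SAP could repair the point, and no section makes the trial's success depend on a secondary endpoint. But the protocol is not silent. It says what will count as statistically significant, and that sentence governs unless it is changed.

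Several further objections stand and limit the size of the point:

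- There is one primary endpoint with its own log-rank test and sample size. The secondary rule does not touch its type I error.
- Duration, pain, opioid and analgesic use, and satisfaction are plausibly positively correlated, so the independent-test figure is the top of the range for a given number of tests.
- The calculation assumes no true difference anywhere. The arms differ by design, with a single injection against a circumferential one, so needle passes and performance time may truly differ. A significant result there need not be false.
- The synopsis does set out its hypotheses before listing further variables, so some separation exists, though it does not reach the analysis section.

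A reader might go further and count sub-items: sensory onset by nerve ("This will be evaluated for supraclavicular, axillary, musculocutaneous, median and ulnar nerve distributions"), day 1 pain at rest and with movement, and each complication. About 25 independent tests would give 1 − 0.95^25 = 0.72. The protocol does not support that figure. It nowhere requires separate tests for these sub-items, it says safety data will be summarised, and Fisher's exact test on rare complications is conservative and would add little.

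**Conclusion.** The point holds as a modest one about how secondary results are interpreted. The protocol fixes an unadjusted 0.05 rule for about 11 to 13 secondary endpoints. If none of them truly differed, the chance of at least one significant result in either direction would be at most about 43% to 49%, the upper figures requiring independent tests. For 13 tests it would be about 24% to 48% over the assumed correlations of 0.7 to 0.1. For a false result in favour of intraplexus it is about 28% with 13 independent two-sided tests. Even the lowest either-direction figure, 24%, is nearly five times the nominal 5%.

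A reader might infer that a false secondary claim is about as likely as not, or that every one of at least 13 endpoints will be tested. Neither follows. The first needs independence, no true difference on any endpoint and a count of 13 or more, and it includes results against intraplexus. The second overlooks that two of the 13 items are also handled as safety data to be summarised. Nor does the rule weaken the primary comparison.

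**What to change.** Replace the sentence in Analysis of Secondary Endpoints. Attach the 0.05 significance rule to the primary endpoint, preferably in Analysis of Primary Endpoint, which at present states no significance level, and say whether it is two-sided. For the secondary endpoints, report estimated differences with 95% confidence intervals and nominal p-values, labelled exploratory.

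If the sponsor wants formal claims on the four hypothesised outcomes (block duration, opioid use, satisfaction, procedure time), name them as a family and prespecify a multiplicity procedure. Holm is one of several acceptable choices. It compares the ordered p-values, smallest first, with 0.05/4 = 0.0125, 0.05/3 = 0.0167, 0.05/2 = 0.025 and 0.05, stopping at the first that fails.

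The change needs no further patients, data or procedures. It costs weaker claims from the secondary endpoints and some loss of power within any adjusted family.

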## Interim Analysis

This study does not entail any sequential or adaptive trial designs and as such, does not require an interim analysis.

## Sample Size and Randomization

The estimated sample size for a two-sample comparison of survivor functions for the primary outcome variable of time to onset of motor block using the Freedman method for log-rank test with a hazard ratio of 0.65, Power of 0.8 and alpha of 0.05, was a total of 208 patients for the two groups, assuming a total number of 172 events.

DATA COLLECTION, RETENTION AND MONITORING

## Data Collection Instruments

The Investigator will prepare and maintain adequate and accurate source documents designed to record all observations and other pertinent data for each subject treated with the study drug.

Study personnel at each site will enter data from source documents corresponding to a subject’s visit into the protocol-specific paper Case Report Form (CRF) when the information corresponding to that visit is available. Subjects will not be identified by name in the study database or on any study documents to be collected by the Sponsor (or designee), but will be identified by a subject number. If a correction is made on a CRF, the study staff member will line through the incorrect data, write in the correct data and initial and date the change.

The Investigator is responsible for all information collected on subjects enrolled in this study. All data collected during the course of this study must be reviewed and verified for completeness and accuracy by the Investigator. A copy of the CRF will remain at the Investigator’s site at the completion of the study.

## Data Management Procedures

The data will be entered into a validated database. The Data Management group will be responsible for data processing, in accordance with procedural documentation. Database lock will occur once quality assurance procedures have been completed.

All procedures for the handling and analysis of data will be conducted using good computing practices meeting FDA guidelines for the handling and analysis of data for clinical trials.

## Data Quality Control and Reporting

After data have been entered into the study database, a system of computerized data validation checks will be implemented and applied to the database on a regular basis. The study database will be updated in accordance with the resolved queries. All changes to the study database will be documented.

## Archival of Data

The database is safeguarded against unauthorized access by established security procedures; appropriate backup copies of the database and related software files will be maintained.  Databases are backed up by the database administrator in conjunction with any updates or changes to the database.

At critical junctures of the protocol (e.g., production of interim reports and final reports), data for analysis is locked and cleaned per established procedures.

## Availability and Retention of Investigational Records

The Investigator must make study data accessible to the monitor, other authorized representatives of the Sponsor (or designee), IRB/IEC, and Regulatory Agency (e.g., FDA) inspectors upon request. A file for each subject must be maintained that includes the signed Informed Consent, HIPAA Authorization and Assent Form and copies of all source documentation related to that subject. The Investigator must ensure the reliability and availability of source documents from which the information on the CRF was derived.

All study documents (patient files, signed informed consent forms, copies of CRFs, Study File Notebook, etc.) must be kept secured for a period of two years following marketing of the investigational product or for two years after centers have been notified that the IND has been discontinued. There may be other circumstances for which the Sponsor is required to maintain study records and, therefore, the Sponsor should be contacted prior to removing study records for any reason.

## Monitoring

Monitoring visits will be conducted by representatives of the Sponsor according to the U.S. CFR Title 21 Parts 50, 56, and 312 and ICH Guidelines for GCP (E6). By signing this protocol, the Investigator grants permission to the Sponsor (or designee), and appropriate regulatory authorities to conduct on-site monitoring and/or auditing of all appropriate study documentation.

## Subject Confidentiality

In order to maintain subject confidentiality, only a subject number will identify all study subjects on CRFs and other documentation submitted to the Sponsor. Additional subject confidentiality issues (if applicable) are covered in the Clinical Study Agreement.

# ADMINISTRATIVE, ETHICAL, REGULATORY CONSIDERATIONS

The study will be conducted according to the Declaration of Helsinki, Protection of Human Volunteers (21 CFR 50), Institutional Review Boards (21 CFR 56), and Obligations of Clinical Investigators (21 CFR 312).

To maintain confidentiality, all laboratory specimens, evaluation forms, reports and other records will be identified by a coded number and initials only. All study records will be kept in a locked file cabinet and code sheets linking a patient’s name to a patient identification number will be stored separately in another locked file cabinet. Clinical information will not be released without written permission of the subject, except as necessary for monitoring by the FDA. The Investigator must also comply with all applicable privacy regulations (e.g., Health Insurance Portability and Accountability Act of 1996, EU Data Protection Directive 95/46/EC).

## Protocol Amendments

Any amendment to the protocol will be written by the principal investigator. Protocol amendments cannot be implemented without prior written IRB/IEC approval except as necessary to eliminate immediate safety hazards to patients. A protocol amendment intended to eliminate an apparent immediate hazard to patients may be implemented immediately, provided the IRBs are notified within five working days.

## Institutional Review Boards and Independent Ethics Committees

The protocol and consent form will be reviewed and approved by the IRB/IEC of each participating center prior to study initiation. Serious adverse experiences regardless of causality will be reported to the IRB/IEC in accordance with the standard operating procedures and policies of the IRB/IEC, and the Investigator will keep the IRB/IEC informed as to the progress of the study. The Investigator will obtain assurance of IRB compliance with regulations.

Any documents that the IRB may need to fulfill its responsibilities (such as protocol, protocol amendments, Investigator’s Brochure, consent forms, information concerning patient recruitment, payment or compensation procedures, or other pertinent information) will be submitted to the IRB. The IRBs written unconditional approval of the study protocol and the informed consent form will be in the possession of the Investigator before the study is initiated.

Protocol and/or informed consent modifications or changes may not be initiated without prior written IRB approval except when necessary to eliminate immediate hazards to the patients or when the change(s) involves only logistical or administrative aspects of the study. Such modifications will be submitted to the IRB/IEC and written verification that the modification was submitted and subsequently approved should be obtained.

The IRB must be informed of revisions to other documents originally submitted for review; serious and/or unexpected adverse experiences occurring during the study in accordance with the standard operating procedures and policies of the IRB; new information that may affect adversely the safety of the patients of the conduct of the study; an annual update and/or request for re-approval; and when the study has been completed.

